**Amendment history**

| **Amendment no.** | **Protocol version no.** | **Date issued** | **Author(s) of changes** | **Details of changes made** |
| --- | --- | --- | --- | --- |
| 1 | 3 | 11/10/2023 | [name] | This amendment seeks to make the following changes:  (i) to collect CYP date of birth and address at baseline; to collect CYP weight throughout treatment  (ii) to deliver the intervention via an online website and interactive PDFs  (iii) to change outcome measure from ChEDE (interview) to EDE-Q (questionnaire)  (iv) to change the optional item of sharing the outcomes of the intervention with an eating disorder service on the consent form to non-optional  (v) to access existing data from services to have same data for everyone  (vi) to make changes to the information sheets in line with changes listed above and other minor changes  (vii) to make changes to the protocol in line with changes listed above and other minor changes |
| 2 | 4 | 17/10/2023 | [name] | This amendment seeks to make the following changes:  (i) to add a parent-reported measure of child eating difficulties (PEDE-Q) at baseline and post-intervention |

**Abbreviations**

| CBT | Cognitive Behaviour Therapy |
| --- | --- |
| CI | Chief Investigator |
| CYP | Children and Young People |
| DSH | Data Safe Haven |
| FBT | Family-Based Therapy |
| GP | General Practitioner |
| GSH | Guided Self-Help |
| ICH | UCL Great Ormond Street Institute of Child Health |
| RCT | Randomised Controlled Trial |

**Study summary**

| Title | Short Psychological Intervention for Children and adolescents with Eating disorders (SPICE) study |
| --- | --- |
| Sponsor name | UCL Great Ormond Street Institute of Child Health |
| Primary objective | To evaluate the feasibility, acceptability and preliminary effectiveness of a guided self-help (GSH) intervention for children and young people (CYP) with eating disorders |
| Study design | Case series |
| Study endpoints | The final follow-up measurement (4 weeks post-intervention) for the final participant |
| Sample size (maximum) | Aim to recruit 10 CYP and their parents/carers |
| Summary of eligibility criteria | CYP  *Inclusion criteria:*   - Aged 8-19 years - Has a threshold or sub-threshold eating disorder (anorexia nervosa, bulimia nervosa, binge eating disorder, other specified feeding and eating disorder [OSFED]) which impairs their psychosocial functioning - UK resident - Has a parent/carer willing to take part in the study   *Exclusion criteria:*   - Does not speak/understand English sufficiently to access the measures and intervention materials - Has an intellectual disability at a level meaning that they cannot access the measures and intervention materials - Acute risk not considered suitable for the study due to the clinical need for immediate and/or specialist intervention (e.g., rapid weight loss, very low mood, high medical or psychiatric risk, acute suicidality, recurrent or potentially life limiting self-harm and/or significant safeguarding concerns) - Unstable psychotropic medication dosage - Receiving other overlapping psychological support - Does not have access to a telephone/computer which can be used for the assessment and guidance sessions   Parents/carers  *Inclusion criteria:*   - Parent/legal guardian of the CYP - UK resident   *Exclusion criteria:*   - Does not speak/understand English sufficiently to access the measures and intervention materials - Has an intellectual disability at a level meaning that they cannot access the measures and intervention materials |
| Intervention | CBT-based Self-help with 8 guidance sessions over 8 weeks |
| Procedures: Screening & enrolment | Families at specialist eating disorder services will be approached by a member of their clinical care team, and eligibility will be determined by a screening questionnaire and an eating disorder questionnaire (Eating Disorder Examination Questionnaire [EDE-Q]) |
| Baseline and outcome measures | Baseline and post-intervention measures:   - Eating Disorder Examination Questionnaire self-report (EDE-Q) and parent-report (PEDE-Q) - Clinical Impairment Assessment (CIA) - %Weight-for-height - Revised Child Anxiety and Depression Scale (RCADS) - DAWBA (baseline only) or SDQ (total and impact supplement)   Session-by-session measures:   - Eating Disorder-15 for Youth (ED-15-Y) - Goal Based Outcomes (GBOs) - Outcome Rating Scale (ORS)/Child Outcome Rating Scale (CORS) - SDQ Session-by-session (SDQ SxS)   Post-intervention measures only:   - Acceptability questionnaire - Optional qualitative interview |
| Treatment period | 3 months maximum |
| End of study | The final post-intervention assessment (12 weeks after baseline measures) for the final participant or the last qualitative interview with the final participant, whichever occurs last |

# Rationale and background information

Eating disorders are disabling conditions that markedly impair physical health and disturb psychosocial functioning (Treasure, 2020). They have high psychiatric and medical comorbidity, and one of the highest rates of mortality among mental health disorders (van Hoeken & Hoek, 2020). Eating disorders can impact substantially on an individual’s health-related quality of life, and are associated with elevated healthcare utilisation and significant economic costs (Ágh et al., 2016; Santomauro et al., 2021). They often begin during adolescence, and are prevalent among those who present to child and adolescent mental health services in the UK (National Collaborating Centre for Mental Health, 2015).

Despite the seriousness of these disorders, access to care for children and young people (CYP) with eating disorders has long been challenging, and this has been exacerbated further by the COVID-19 pandemic (Spigel et al., 2021). The COVID-19 pandemic has adversely affected CYP with eating disorders, with an increased incidence of a first diagnosis and deteriorating symptoms among those with pre-existing diagnoses (Katzman, 2021). Child and adolescent eating disorder services in the UK have seen almost a doubling in the number of referrals (NHS England, 2023), and it is estimated that 60% of young people aged 17-19 have disordered eating (Newlove-Delgado, 2022). NHS services have struggled to meet this increased demand for treatment, with only 68% of urgent and 69% of routine cases seen within the standard (a target of 95%) during April-June 2022 (National Audit Office, 2023). This is concerning given that delays in receiving specialist treatment can increase the risk of chronicity and burden of illness (Striegel Weissman & Rosselli, 2017). This demand-capacity gap highlights the urgent need for less resource-intensive interventions which are scientifically supported, accessible and scalable for this patient group, such as guided self-help.

Guided self-help interventions are the first step treatment for adults with bulimia nervosa and binge eating disorder (National Institute for Health and Care Excellence, 2017), and have proven efficacy for CYP with anxiety and depression (Bennett et al., 2019; Thirlwall et al., 2013), which often co-occur with eating disorders (Keski-Rahkonen & Mustelin, 2016). However, child and adolescent eating disorder services do not routinely use guided self-help interventions as they have not been sufficiently researched. The limited research that does exist suggests that guided self-help interventions have the potential to be effective for this patient group. In their randomised controlled trial (RCT), Schmidt et al. (2007) compared cognitive behavioural therapy (CBT) guided self-care with family therapy in 85 adolescents with bulimia nervosa and related disorders, and the outcomes indicated no difference between groups, with the guided self-care showing greater impact at 6 months and being more cost-effective. Lock et al. (2021) conducted a pilot RCT of 40 adolescents with anorexia nervosa which compared online family-based guided self-help to family-based treatment delivered via videoconferencing. The results suggested that family-based guided self-help was acceptable to families and led to improvements in terms of both weight gain and global eating disorder psychopathology. However, both of these interventions remain in the domain of research and are not readily available for CYP with eating disorders in the UK.

# Objective and purpose

The overarching aim of this project is to improve access to psychological treatments for CYP affected by eating disorders. Specifically, this preliminary study aims to examine the feasibility, acceptability and preliminary effectiveness of a guided self-help intervention for CYP (aged 8-19 years) with impairing symptoms of eating disorders.

# Theoretical framework

The development and evaluation of this intervention will be considered within the Medical Research Council’s (MRC) updated framework for the development and evaluation of complex interventions (Skivington et al., 2021). The framework divides research of complex intervention into four distinct, but not necessarily sequential, phases: development/identification of the intervention; feasibility; evaluation; and effective implementation (see Figure 1 below). This study will predominantly focus on the feasibility and preliminary evaluation aspects of this framework.

**Feasibility**

Assessing feasibility and acceptability of intervention and evaluation design in order to make decisions about progress to next stage of evaluation

**Evaluation**

Assessing an intervention using the most appropriate method to address research questions

**Implementation**

Deliberate efforts to increase impact and uptake of successfully tested health interventions

**Core elements**

- Consider context
- Develop, refine and (re)test programme theory
- Engage stakeholders
- Identify key uncertainties
- Refine intervention
- Economic considerations

**Develop intervention**

Developing a new intervention, or adapting an existing intervention for a new context based on evidence base and theory of the problem

**Identify intervention**

Choosing an intervention that already exists (or is planned), either via policy or practice, and exploring its options for evaluation (evaluability assessment)

**OR**

Figure 1: Medical Research Council Framework for the development and evaluation of complex interventions (Skivington et al., 2021)

# Methods

## Study setting

The main research sites identified for this project are specialist child and adolescent eating disorder services across the UK.

## Study design

This study will employ a case-series design in which CYP with impairing eating disorder symptoms, and their parents/carers, will receive a self-help intervention and 8 x 30-minute guidance sessions via videocall or telephone over a period of 8 weeks. Standardised assessments will be administered at baseline and posttreatment, and on a weekly basis throughout the intervention. The feasibility, acceptability and preliminary treatment effects will be specifically examined.

## Participants

This study will look to recruit CYP (aged 8-19 years) with impairing symptoms of eating disorders, and their parents/carers. In line with previous case series research (da Luz et al., 2017; Dumont et al., 2019), the aim will be to recruit approximately 10 eligible families to receive the CBT guided self-help intervention.

**Eligibility criteria**

### Children and young people

Inclusion criteria

The inclusion criteria for CYP:

1. Aged 8-19 years
2. Has a threshold or sub-threshold eating disorder (anorexia nervosa, bulimia nervosa, binge eating disorder and otherwise specified feeding and eating disorder [OSFED]) which impairs their psychosocial functioning
3. Is a UK resident
4. Have a parent/carer who is also willing to take part in the study

Exclusion criteria

The exclusion criteria for CYP:

1. Does not speak/understand English sufficiently well to access the measures and intervention materials. This is primarily due to limited funding capacities for interpreters
2. Has an intellectual disability at a level meaning that they cannot access the measures and/or intervention. This will not be defined by IQ, but by clinical judgement. CYP will not be excluded because of the presence of intellectual disability per se, but because of being unable to access the materials. Ability to participate may be different for younger children who are less able, whose parents complete the materials, compared to older children who need to complete the materials themselves. If the intellectual disability is identified during the initial assessment (through clinical judgement), young people will be referred to other more appropriate services as necessary (with agreement of the family)
3. Questionnaire indicates acute risk not considered suitable for the trial due to the clinical need for immediate and/or specialist intervention, e.g., rapid weight loss, very low mood, high medical or psychiatric risk, acute suicidality, recurrent or potentially life limiting self-harm and/or significant safeguarding concerns (i.e., if the child has a child protection plan and/or is on the child protection register, and/or the research team consider the child to be suffering, or likely to suffer, significant harm)
4. If they have been prescribed psychotropic medication, the dosage must have been stable for the past two months
5. Currently receiving other overlapping psychological support/interventions
6. Does not have access to a telephone or laptop/computer which can be used for the interviews and guidance sessions

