## Procedure

### Recruitment and informed consent of participants

Specialist child and adolescent eating disorder services in the UK have been identified as research sites for this project. [name] will obtain honorary contracts at each research site for research activity.

CYP, and their parents/carers, will be contacted by a member of their clinical care team at the site in question. The member of the patient’s clinical care team will provide an overview of the study and will ask families if they would like to receive the study information (i.e., participant information sheet).

If the family agree to receive a participant information sheet, the member of the clinical team will provide this to the family (either electronically or in a paper copy). The information sheet will contain the contact details of the research team so that the CYP, and/or their parents/carers, can contact the research team to ask any questions they may have. The information sheet will also contain a QR code to an online form that potential participants can fill in to share their contact details with the research team to enable the research team to contact them directly.

The member of the clinical team will also ask families for explicit written or verbal consent for their contact details to be held by the research team going forwards. The member of the clinical team will sign a ‘consent to be contacted by the research team’ form to confirm whether written or verbal consent has been obtained by the family for their contact details to be held by the research team.

After a reasonable period of time, the family will be contacted by the study researcher and asked if they have any questions about the study and/or are interested in taking part. Once they have decided to take part, the researcher will gain informed consent/assent via an online consent/assent form. Parents/carers and CYP (aged ≥ 16) will be asked to provide informed consent to participate in the study, and CYP (aged < 16) will be asked to provide assent, in addition to the consent of their parent/carer.

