### Screening and eligibility assessment

Once families have been recruited through one of the recruitment sites, and have completed the study consent/assent forms, their eligibility for the research will be confirmed.

Families who consent/assent to participate in the study will be asked to complete a short screening questionnaire to determine their eligibility for participation (see [Appendix 1](#Appendix1)). This will include demographic information about the CYP and their parent(s)/carer(s), confirmation of UK residency, information about prescribed psychotropic medication of the CYP, current/previous psychological support received by the CYP, brief questions to determine if the CYP is experiencing possible symptoms of eating disorders that impair their functioning and a question around current self-harm and suicidality. This questionnaire can be completed online or via telephone with the study researcher. It is expected that this questionnaire will take approximately 15 minutes to complete. If families are not eligible for the study, the study researcher will contact the family to explain why they are not eligible for the research, and signpost them to relevant support, as necessary. If the screening questionnaire indicates that the family meet the eligibility criteria, they will be invited to enrol in the study.

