### Procedure once participants are enrolled

Once participants are enrolled into the study, CYP and their parents/carers will be invited to complete the baseline measures, including a battery of questionnaires, including the self-report of the Eating Disorder Examination Questionnaire [EDE-Q] and the parent-report of Eating Disorder Examination Questionnaire [PEDE-Q]). This is to confirm that the intervention is appropriate (i.e., that the CYP has impairing symptoms of eating disorders and an absence of significant risk as detailed in the inclusion/exclusion criteria). Families may also be asked to complete the online Development and Wellbeing Assessment (DAWBA) to enable an understanding of comorbid diagnoses. Note – the DAWBA will be piloted with families in the first instance. If the family have already completed the DAWBA during their assessment with the eating disorder service, this data will be accessed to prevent duplication of measures. Following the pilot, it may be decided to no longer use the DAWBA, and families will be asked to complete the Strengths and Difficulties Questionnaire (SDQ) at baseline instead.

Questionnaires will be sent to families to complete online (or over the telephone if preferred). The questionnaires will cover some additional demographic information about the family ([Appendix 2](#Appendix2)), brief questions about the CYP’s eating disorder symptoms and how they impair their functioning, and symptoms of anxiety and depression. They will also be asked to report on the CYP’s current weight and height. It is expected that these questionnaires will take approximately 15 minutes to complete. Families may also complete the DAWBA online (or over the telephone with a researcher if preferred) which will take around 45 minutes to complete.

Families will then be invited to attend a feedback appointment where the study researcher will feed back the information obtained from the questionnaires, and to discuss next steps regarding the intervention. This feedback appointment is likely to last around 30 minutes. The family will be given a report summarising the outcomes of the questionnaires and the next steps for treatment. The family’s GP and other teams involved in their care (e.g., eating disorder service) will also be sent a copy of this report to inform them about the family’s participation in the study.

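### Exclusion criterion 3 depends on what a questionnaire shows, but no screening form asks about weight change, medical concerns or child-protection status, and no other pre-treatment step is set up to ask

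*Protocol*

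**What the plan says.** In the Protocol, Eligibility criteria (Children and young people), exclusion 3 applies when "Questionnaire indicates acute risk not considered suitable for the trial due to the clinical need for immediate and/or specialist intervention, e.g., rapid weight loss". Its other examples include high medical risk and significant safeguarding concerns. The safeguarding limb is met "if the child has a child protection plan and/or is on the child protection register", or when the research team judges that the child is at risk of significant harm.

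The Study summary states that "eligibility will be determined by a screening questionnaire and an eating disorder questionnaire", the second being the EDE-Q. The section Screening and eligibility assessment makes the first of these the gate: "If the screening questionnaire indicates that the family meet the eligibility criteria, they will be invited to enrol in the study". After enrolment, the baseline measures are meant to confirm, among other things, "an absence of significant risk as detailed in the inclusion/exclusion criteria". On weight, that step says: "They will also be asked to report on the CYP’s current weight and height".

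Under Recruitment and informed consent of participants, the clinical team member introduces the study, provides the information sheet and signs a form "to confirm whether written or verbal consent has been obtained by the family for their contact details to be held by the research team". That section also says: "The information sheet will also contain a QR code to an online form that potential participants can fill in to share their contact details".

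**The concern.** A criterion worded around what a questionnaire shows works only if some questionnaire asks for the fact. Two of the conditions named, weight loss and medical risk, matter directly to physical safety in a study open to children from age 8, including those with anorexia nervosa. The third, a child protection plan or register entry, is a matter of record that somebody has to ask about.

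If no step asks, staff can follow the protocol exactly and still enrol a child it means to exclude. The intervention is delivered by video or telephone, and Appendix 5 says the research team does not hold clinical responsibility for the family. That makes the check before treatment more important.

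**Working it through.** There is no stated figure to reproduce. The check sets the criterion against each form and each step before treatment.

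**Screening forms (Appendices 1a, 1b, 1c)**

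| Fact named in criterion 3 | 1a (parent) | 1b (over 16) | 1c (under 16) |
| --- | --- | --- | --- |
| Recent weight change | not asked | not asked | not asked |
| Current medical concerns | not asked | not asked | not asked |
| Child protection plan or register | not asked | not asked | not asked |

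3 facts × 3 forms = 9 checks; items found = 0. What the forms do contain:

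- Risk questions: 1 per form, on thoughts of self-harm or suicide.
- Numbered health questions: 6 (1a) + 6 (1b) + 0 (1c) = 12. They cover eating disorder and other mental health diagnoses, treatment, waiting list and psychotropic medication; 0 of 12 concern physical health.
- ChEDE-Q8: 5 of 8 items mention weight (restraint, food avoidance, wish to lose weight, guilt, dissatisfaction). All concern attitude or intent; 0 ask whether weight has changed. The adapted SDQ impact question mentions body weight only as an area of difficulty.
- Open comment box: on 2 of 3 forms (1a and 1b). Form 1c has none, although the parent's form 1a covers the same child.

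The prose in Screening and eligibility assessment lists the same content, so this is not a gap created by how the forms were extracted.

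**Other steps before treatment**

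- Baseline weight: a change is weight now minus an earlier weight. Baseline supplies only the first term, so no change can be derived.
- Appendix 2: 5 demographic fields + 4 on the parent's own health (2 questions, 2 follow-ups) = 9 fields; 0 cover the three facts.
- EDE-Q: described under Measures as covering eating disorder attitudes and behaviours. Its items, and those of the PEDE-Q and DAWBA, are not shown and were not counted. The DAWBA may be dropped after the pilot.
- Service records: the amendment history mentions access to existing service data in general, but the current procedure names only a DAWBA already completed there.
- Referring clinician: introduces the study and records consent to contact; no eligibility or risk check is assigned.
- Feedback appointment: reports questionnaire results and discusses next steps; it is not described as gathering these facts.

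**Later safeguards**

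Appendix 5 (sections 4.2 and 4.4) says risk questions are not routinely asked in structured contacts or guidance sessions. The Appendix 5a prompt sheet is used once something has been disclosed. Weekly weights are listed with the session-by-session measures, so they begin with treatment.

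**The case against.** The strongest reply is that criterion 3 says questionnaire, not screening questionnaire, and that baseline is a second check intended to confirm absence of the excluded risks. Some unseen EDE-Q, PEDE-Q or DAWBA item might ask about weight loss, and %weight-for-height from the baseline weight is a partial marker of medical risk. That stands as a limit on the weight and medical limbs. It does not reach child-protection status, which lies outside the described scope of every listed measure.

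Second, recruitment starts in specialist eating disorder services, whose clinicians probably know these facts. The GP and the service are also sent a report after baseline, so a warning could come back without the family raising it. But the report tells them the family is taking part; it does not ask for the three facts, and its timing against the first session is not fixed.

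Third, rapid weight loss and medical risk are examples of a clinical judgement, and part of the safeguarding limb is the team's own view. True, but a judgement needs information, and plan or register status is a plain fact.

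Fourth, the 9 checks are not nine separate faults, since the forms overlap; the gap is three facts.

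Finally, about 10 families are planned, with weekly weights, weekly supervision and withdrawal for significant risk. These limit harm once treatment is under way, but do not apply the exclusion beforehand.

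**Conclusion.** The concern holds and should be fixed. Three facts named in criterion 3, or needed to apply it, are asked on none of the three screening forms, and no other step before treatment is described as asking for them as a rule. They might still surface through the open box, the feedback appointment, a disclosure handled under Appendix 5, or a reply to the report sent to the GP and service, but nobody is instructed to ask.

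The conclusion rests on the forms as printed and the procedures as described. It is firmest for child-protection status. For weight change and medical concerns it is subject to the content of instruments not shown. The protocol gives no figure for how often an excluded child would be missed, and none is claimed here. A statistical analysis plan would not close the gap, because the forms are part of the protocol.

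**What to change.** Add three items to Appendix 1: recent weight change, current medical concerns, and child protection plan or register status. The parent form 1a is the natural place, since it covers the child under 16 as well.

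Alternatively, have the referring clinical team confirm the three facts in writing before treatment starts. The form item is the sturdier route, because it sits where eligibility is decided and families may send their own contact details by QR code. That second reason is modest: the clinician still hands over the sheet carrying the code.

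Either way, reword criterion 3 to name the chosen source. What counts as rapid weight loss or high medical risk is for the clinical supervisors to set.

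The cost is about three form fields, or a few lines for the referring team, plus one wording change. The downside is an ethics amendment and a small extra task for the parent or clinician.
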